### Participants

#### Recruitment

The population base from which the subjects will be drawn are Dutch adult cancer survivors, meeting in/exclusion criteria. A website is created, containing information on the study and the possibility to enrol as a participant. Collaboration with Dutch patient organizations is sought and all (social) media channels available will be utilized to ensure recruitment of the planned number of participants. Other recruitment strategies will include: reaching out to smoking cessation clinics, oncology nurses and meeting centers for cancer survivors, online advertisements on (health-related) websites, targeted facebook and search engine campaigns, and advertisements in newspapers and magazines relevant to the target group.

#### In- and exclusion criteria

All potential participants fill out an online screening questionnaire to determine whether they fulfil all inclusion criteria and none of the exclusion criteria. There are four possible outcomes: 1) inclusion criteria are not met and applicants cannot participate in the study; 2) inclusion criteria for the alcohol RCT are met and they are invited to participate in the alcohol RCT, 3) inclusion criteria for the tobacco RCT are met and they are invited to participate in the tobacco RCT, 4) inclusion criteria for both RCTs are met and participants can choose in which one of the two RCTs they want to participate (they cannot participate in both RCTs). Participants who do not fulfil criteria for inclusion will be provided with links to websites with further alcohol/smoking information and help.

Shared inclusion criteria (for both RCTs):Age 18+Diagnosis of any form of cancer in the last 10 yearsPC and internet connection available at homeAbility and intention to participate in the study and the intervention during the period of one yearInformed consent provided

Additional inclusion criteria for the AM RCT only:Alcohol consumption of > 7 standard drinking units (10 g of ethanol) in the last 7 daysIntention to reduce or quit alcohol use as assessed by one item from the screening questionnaire

Additional inclusion criteria for the SC RCT only:Cigarette use of > = 5 cigarettes per day in the last 7 daysIntention to quit smoking cigarettes as assessed by one item from the screening questionnaire

Shared exclusion criteria (for both RCTs):Insufficient mastery of Dutch languageSelf-reported suicidal ideation, acute psychosis, severe alcohol dependence, dementia, severe depressionSelf-reported pregnancy

### Sample size

For both the AM RCT and SC RCT, conventional power (1-beta = .80) and levels of statistical significance (alpha = .05) are chosen. For both trials, the primary outcome data is collected at 6 months post-randomisation.

For the AM RCT, the primary outcome variable is based on the 7-day TLFB alcohol measurement, 6 months post-randomisation. Based on the average of 2 previous RCTs on very similar self-help interventions in the Netherlands versus a control condition (see Riper 2008 and Blankers 2011 in [25]), a Cohen’s d effect size of d = 0.40 is expected. Using the power calculation package “pwr” [41] for R 3.0.1 [41], d = .40 translates into a minimum net sample size of 2 × 99 participants in case of 2-sided testing, or 2 X 78 participants in case of 1-sided testing. Assuming a maximum of 25% non-response at 6 months follow-up, we intend to include 99 × 2 x (100/(100–25)) = 264 (or 208 for 1-sided testing) participants in the alcohol RCT. In case the drop-out rate is lower than 25%, power will be somewhat higher than we anticipate in this calculation, i.e. in that case we are more likely to find a true effect.

For the SC RCT, the primary outcome variable is based on the 7-day TLFB smoking measurement: self-reported abstinence in the last 7 days prior to the primary measurement point, 6 months post-randomisation. Based on a study by Duffy et al. amongst cancer survivors [12], a quit-rate of 30% in the active smoking cessation intervention group, vs 15% in the smoking cessation control group can be expected. This translates into a relative risk (RR) of 2.14, which is comparable to the RR estimate in a recent Cochrane review (RR = 2.05) [26]. Based on a pilot trial of an ACT smoking cessation internet intervention [42], a 23% quit rate in the experimental arm vs a 10% quit rate in the control arm can be expected (RR = 2.20), at the 3 months follow-up. Based on the average of these RRs, a RR = 2.1 is expected. This translates into a 21% quit rate in the experimental condition, assuming a 10% quit rate in the control condition at 6 months post-randomisation. Using “pwr” [43] for R 3.0.1 [41], a 21% quit-rate vs 10% quit-rate translates into a net sample size of 2 × 157 participants, based on 2-sided tests (2 X 124 for 1-sided tests). Assuming 25% non-response at 6 months follow-up, we need 157 × 2 x (100/(100–25)) = 419 participants in the SC RCT for 2-sided tests, and 331 for 1-sided tests).

The described power analyses are conservative. We may perform half-way post-hoc power analyses for both RCTs, based on those we will evaluate our assumptions underlying these power calculations and may adjust the sample sizes if necessary. We might for example not fully compensate the expected 25% drop-out, as drop-out rates might be lower and we will perform intention-to-treat analyses including multiple imputation, which partially recovers power. One-sided testing is mentioned because it is very plausible that the interventions will have a positive effect on SC and AM [25, 26, 42]. Furthermore, within the above mentioned calculation, clustering of measurements (baseline, 3-, 6- and 12-months) within participants and related covariance has not been taken into consideration. Accounting for this could also change required sample sizes.

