### Randomisation

After completing the baseline measurement, participants will be allocated to the two trial arms in a 1:1 ratio. As the number of participants we aim to include in each trial arm is not very large, random variation in baseline characteristics could reduce trial arm equivalence. Therefore, allocation through adaptive randomisation (Minimisation [39, 40]) will be used to balance trial arms with regard to age, sex, and education level. Adaptive randomisation implies that the randomisation sequence is not a priori known but is based on the variance in variables that need to be balanced over the trial arms. If imbalance between the trial arms in age, sex or education occurs, the probability of allocation to the trial arm that minimizes this imbalance is increased to 0.67 (instead of 0.5). The randomisation procedure is automatized and performed by triggering a server-sided PHP script using a Mersenne twister random number generator, immediately after the participant has completed the baseline measurement. After randomisation, the participant is informed about the outcome of the randomisation via an automated email, and assigned to one of the two conditions via an automated server-sided computer script. After this assignment, the researchers are informed about the outcome and assignment of the participant via an automated registration in the trial management database. As this is an open label RCT, the participants nor the researchers are blinded regarding the allocated conditions.

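### Smoking-cessation trial: the printed quit rates of 21% vs 10% require 165 per arm, not 157; at 157 per arm the power is about 78%, not 80%

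*Protocol article*

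**What the plan says.** The Sample size section sets the design values for both trials: "conventional power (1-beta = .80) and levels of statistical significance (alpha = .05) are chosen". For the smoking-cessation (SC) trial it builds the planning effect from three sources:

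- a study among cancer survivors, with 30% vs 15% quitting: "This translates into a relative risk (RR) of 2.14";
- a Cochrane review, with a relative risk (RR) of 2.05;
- a pilot trial of an internet intervention based on acceptance and commitment therapy, with 23% vs 10%, where the "quit rate in the control arm can be expected (RR = 2.20").

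The average of these is given as 2.1, which with a 10% control rate becomes 21%. Then "a 21% quit-rate vs 10% quit-rate translates into a net sample size of 2 × 157 participants". That figure is for two-sided testing; the one-sided alternative is put at 124 per arm. The allowance for non-response follows: "157 × 2 x (100/(100–25)) = 419 participants in the SC RCT for 2-sided tests". The corresponding one-sided target is 331. The Randomisation section fixes equal allocation: "participants will be allocated to the two trial arms in a 1:1 ratio". The Sample size section goes on to say of both trials: "The described power analyses are conservative".

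**The concern.** A reader who enters the printed rates, alpha and power into the named package does not get the printed size, two-sided or one-sided. Two of the RRs behind the 21% also differ from the ratio of the rates printed next to them. This is the sample-size justification for the SC primary outcome. If the printed rates are the planning assumption, the trial is sized slightly below its stated power. If a different rate was used, the article does not state the effect the trial was powered to detect.

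**Working it through.** **Inputs** (Sample size section; allocation from Randomisation): quit rates 0.21 and 0.10, alpha .05, power .80, 1:1 allocation, 25% non-response, R package pwr, which uses the arcsine effect size for two proportions.

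**1. The plan's figure from its printed rates.**
h = 2·asin(√0.21) − 2·asin(√0.10) = 0.3086.
n per arm = 2·((z_alpha + z_power)/h)².
- Two-sided: 2·((1.960 + 0.842)/0.3086)² = 164.87, so 165. Stated: 157.
- One-sided: 2·((1.645 + 0.842)/0.3086)² = 129.87, so 130. Stated: 124.

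Other two-sided formulas give more, not less: unpooled normal 166, pooled normal 169, log odds ratio 177, log relative risk 182, continuity-corrected 187. The choice of method does not explain 157.

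**2. Non-response.** The inflation step is done correctly: 2 × 157/0.75 = 418.7, so 419. It therefore carries the discrepancy straight through. From the printed rates the targets are 2 × 165/0.75 = 440 and, one-sided, 2 × 130/0.75 = 346.7, so 347.

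**3. Power at the stated size, 21% vs 10%, two-sided.** Arcsine: Φ(0.3086·√(157/2) − 1.960) = 78.1%. Pooled normal: 77.1%. Exact enumeration of the uncorrected chi-square test: 77.6%.

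**4. Where 157 and 124 probably come from.** The mean of the three printed RRs is (2.14 + 2.05 + 2.20)/3 = 2.13, i.e. 21.3% vs 10%. That gives 157.29 two-sided and 123.90 one-sided, which are both printed figures to the nearest integer. Solving backwards with 10% in the control arm, n = 157 needs 21.31% and one-sided n = 124 needs 21.29%. This origin is an inference; the article does not state it.

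**5. The RRs against their own rates.**

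| Printed rates | Ratio | Range if rates are rounded to whole percent | Printed RR |
|---|---|---|---|
| 30% vs 15% | 2.00 | 29.5/15.5 = 1.90 to 30.5/14.5 = 2.10 | 2.14 |
| 23% vs 10% | 2.30 | 22.5/10.5 = 2.14 to 23.5/9.5 = 2.47 | 2.20 |

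The 2.14 lies outside what rounding allows. The 2.20 lies inside it.

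**6. Effect of recomputing the RRs from the printed rates.** (2.00 + 2.05 + 2.30)/3 = 2.117, which still rounds to 2.1. Unrounded, 21.17% vs 10% gives 160.5, so 161 per arm, or 2 × 161/0.75 = 429.3, so 430 randomised.

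**7. Alcohol trial, for comparison.** d = 0.40 gives 99.08 two-sided and 77.97 one-sided, against 99 and 78 printed; 2 × 99/0.75 = 264. This reproduces.

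**The case against.** The strongest defence is that the calculation was run correctly on unrounded values and only the display was rounded. The text says the planning RR is the average of the RRs it lists, and that average reproduces both SC sizes. The alcohol sizes are rounded to the nearest integer in the same way. On that reading, power at 157 per arm is 79.9%. This stands as the likely explanation, and it rules out saying that nothing in the article leads to 157. It does not make the sentence right: the size is attributed to 21% vs 10%, and the 21.3% behind it depends on an RR of 2.14 that its own rates contradict.

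A reader might infer more, and the documents do not support it:

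- **That both RRs are miscalculated and should read 2.00 and 2.30.** Only 2.14 is firmly inconsistent. Since 30/14 = 2.14, the misprint could equally be in the 15%. The cited sources are needed to decide.
- **That the RR discrepancies cause the shortfall.** They nearly cancel; the mean still rounds to 2.1. The gap from 165 to 157 comes from 21% against 21.3%.
- **That small effects elsewhere in the article refute the claim of conservatism.** The RR of 1.27 concerns motivational interviewing in general. The 16.5% vs 15.5% compares web with print versions of one programme. The small pooled effect is for alcohol interventions. None is this intervention against a static brochure. The section also ties its claim to drop-out compensation, imputation and one-sided testing, which this check does not address.

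It is also fair that the section allows the assumptions to be reviewed half-way and the size adjusted. That limits the practical harm but does not correct the printed figure.

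**Conclusion.** The point holds as a discrepancy in the SC sample-size statement. With the printed rates, two-sided alpha .05, 80% power, equal allocation and the arcsine method, the size is 165 per arm and 440 in total, not 157 and 419; one-sided it is 130 and 347, not 124 and 331. Taking 21% vs 10% literally, the stated size gives 77% to 78% power, depending on the method. The shortfall is 8 per arm, or 21 on 440 randomised (about 5%), and 2 points of power. It does not show a materially underpowered trial, and it does not reach the alcohol trial.

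Separately, RR 2.14 contradicts 30% vs 15%, while RR 2.20 is only apparently at odds with 23% vs 10%. A size slightly below what its own printed rates require cannot be called conservative on the strength of those rates.

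**What to change.** 1. Check the 30%/15% and 23%/10% quit rates and the RRs 2.14 and 2.20 against their sources, and print rates and RRs that agree.
2. Then do one of the following:
   - keep 419 and state that 157 per arm gives about 78% power for 21% vs 10%; or
   - print the rate actually used, with a valid derivation, and the size that follows from it. For example, 21.3% gives the present 157 if the three RRs are confirmed; RRs recomputed from the printed rates give 161 per arm and 430 in total.
3. Bring the one-sided figures into line in the same way.
4. Limit the statement that the power analyses are conservative so that it does not rest on the SC quit rates.

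The cost is a text correction and a check of the cited sources. Keeping 419 needs no further participants; the only price is a slightly lower stated power.

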Based on recent systematic reviews of RCTs among people who smoke or drink excessively, there is accumulating evidence that guided and unguided internet-based interventions for alcohol moderation (AM) [25] and smoking cessation (SC) [26] can be effective, but also leave room for improvement as effect sizes tend to be small. For internet-based alcohol interventions in particular, a recently published meta-analysis, including a total of 16 randomised controlled trials (with 23 comparisons and 5612 participants), showed a small but significant overall effect size in favour of internet interventions, compared to waitlisted participants, information brochures, or assessment only, but this effect is not sustained after 12 months [25]. A paper integrating all recent reviews on this topic came to similar conclusions [27]. In a Cochrane review on internet-based SC interventions, 28 randomised or quasi-randomised trials were included, yielding data from over 45,000 participants. Results were mixed. All in all, internet-based interventions for SC show some positive results for the general population, but leave room for improvement beyond the standard CBT-based internet interventions [26]. A rather new promising therapeutic approach is Acceptance and Commitment Therapy (ACT), part of third-wave CBT. Both therapeutic approaches have shaped the interventions described in this paper, which will be elaborated further in the intervention descriptions.

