Although the potential of internet-based interventions to improve lifestyle factors among cancer survivors is recognized [28], most of currently reported interventions target diet and physical exercise [29]. In a recent study, Bantum et al. [30] tested the effectiveness of a six-week Web-based multiple health behaviour change program for adult survivors compared to a waitlist condition in an RCT (*n* = 352). Cancer survivors were eligible if they had completed their primary cancer treatment from 4 weeks to 5 years before enrolment. The web-based intervention positively impacted reduction of insomnia and frequency of exercise [30]. Further, a web-based, tailored SC program for young adult and childhood cancer survivors yielded positive SC outcomes at 15 months post-randomisation in an RCT comparing web and print-based materials. Both versions yielded quit rates (*n* = 374, web-based: 16.5%, print-based: 15.5%) that are similar to the intensive telephone counselling treatment they were based on (15% at 12 months post-randomisation) [31].

Thus far, specific AM and SC internet-based intervention RCTs have not been focused specifically on cancer survivors, with a few exceptions [31, 32]. There is a lack of knowledge on what results in terms of effectiveness and cost-effectiveness could be obtained when existing internet interventions for smoking and alcohol would be tailored to cancer survivors. Based on (Cochrane) reviews on other lifestyle interventions, positive outcomes can be expected [28, 30, 33–35]. Furthermore, time of diagnosis is referred to as a ‘teachable moment’ [36, 37]; cancer diagnosis might trigger cancer survivors and possibly their family members [37] to adapt a more healthy lifestyle and may thus be a good moment to introduce health promotion programs.

The objective of the two RCTs presented in the current study protocol is to test the effectiveness of two newly developed online interventions to reduce alcohol use or tobacco smoking in samples of excessive drinking or smoking cancer survivors.

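### The sample size section calls the power analyses conservative, but they hold no margin at the planned effects, and the text offers to give up the only cushion, the drop-out allowance

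*Protocol article*

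**What the plan says.** The Sample size section sets "conventional power (1-beta = .80") and "levels of statistical significance (alpha = .05) are chosen", with two-sided sizes given first and one-sided sizes as an alternative. The Randomisation section adds that "participants will be allocated to the two trial arms in a 1:1 ratio".

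- **Alcohol trial:** d = 0.40, "Based on the average of 2 previous RCTs on very similar self-help interventions in the Netherlands versus a control condition". Both trials come from the alcohol meta-analysis cited in the Background. The result is 2 × 99 analysed, or 264 randomised after allowing for 25% non-response.
- **Smoking trial:** 21% versus 10%, from an expected relative risk of 2.1. The result is 2 × 157 analysed, or 419 randomised.

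The closing paragraph of that section states that "The described power analyses are conservative". It allows a half-way review that may change the sample sizes, and gives one example: "We might for example not fully compensate the expected 25% drop-out". Its reasons are that drop-out may be lower and that multiple imputation recovers part of the power. It adds that repeated measures were left out of the calculation.

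The Background says of internet interventions for both behaviours that they "can be effective, but also leave room for improvement as effect sizes tend to be small". It also describes the pooled effect in the alcohol meta-analysis (16 trials, 5612 participants) as small, without a figure.

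**The concern.** A power analysis is conservative when its assumptions are less favourable than the evidence suggests, so that true power probably exceeds the nominal value. Here both trials are sized for the effect that is expected, with no discount. For alcohol, that effect comes from two selected trials in a body of evidence the protocol itself calls small overall.

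The label matters because of where it stands: it opens the paragraph that then contemplates under-compensating drop-out. A reader, funder or ethics committee would take it that there is power to spare. If there is none, using that option brings the trials below their stated 0.80 even when the planned effects are true.

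**Working it through.** **Inputs (Sample size section).** Two-sided alpha 0.05, target power 0.80, 1:1 allocation; alcohol d = 0.40; smoking 21% versus 10%; drop-out 25%. The section names the R package pwr, so I use its methods: the t-test for means and the arcsine effect size for proportions.

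**1. Alcohol trial, reproducing the plan.** The two-sample t-test at d = 0.40 and 80% power needs 99.08 per arm, printed as 99. Then 99 × 2 / 0.75 = 264. This reproduces. Power at 99 per arm is 0.800, which is the nominal value with nothing above it.

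**2. Smoking trial, reproducing the plan.**
- h = 2·arcsin(√0.21) − 2·arcsin(√0.10) = 0.9521 − 0.6435 = 0.3086.
- n per arm = 2 × ((1.960 + 0.842) / 0.3086)² = 164.9, so 165, not 157. The pooled normal formula gives 169.
- Power at 157 = Φ(0.3086 × √(157/2) − 1.960) = Φ(0.774) = 0.781. The pooled formula gives 0.771.
- The mean of the three printed relative risks is (2.14 + 2.05 + 2.20) / 3 = 2.13, which is 21.3% on a 10% control rate. There h = 0.3159 and n = 157.3, so the printed 157 appears to rest on 21.3% that was rounded in the text.
- The drop-out step is correct: 157 × 2 / 0.75 = 418.7, so 419.

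**3. The drop-out cushion.** If nobody dropped out of the alcohol trial, 264 / 2 = 132 per arm would be analysed. Power would be 90% at d = 0.40 and 81% at d = 0.35.

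**4. What is lost if drop-out is not compensated and the planned 25% occurs.**

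| Trial | Randomised | Analysed per arm | Power at planned effect |
|---|---|---|---|
| Alcohol | 198 | 198 × 0.75 / 2 ≈ 74 | 68% |
| Smoking | 314 | 314 × 0.75 / 2 ≈ 118 | Φ(0.3086 × √59 − 1.960) = Φ(0.410) = 66% |

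This is the limiting case. Partial compensation falls between these figures and those in steps 1 and 2.

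**5. Sensitivity to a smaller effect.** The documents put no number on small, so these values are assumptions that show a range, with full drop-out compensation and 25% lost.

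| Alcohol, 99 per arm | Power | Smoking, 157 per arm | Power |
|---|---|---|---|
| d = 0.40 (planned) | 80% | 21% vs 10% (planned) | 78% |
| d = 0.35 | 69% | 18% vs 10% | 54% |
| d = 0.30 | 56% | 15% vs 10% | 27% |
| d = 0.20 | 29% | | |

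**The case against.** The strongest reply is that the label is about drop-out, imputation and repeated measures, since those are the topics that follow it, and not about effect size. The alcohol text does call 25% a maximum, and lower drop-out would add real power (step 3). This stands in part: drop-out is a genuine cushion. But it is the same cushion the example proposes to spend, so it cannot also justify the label. On imputation the section claims only partial recovery of power, and on repeated measures it says only that the required sizes could change, without a direction.

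A second reply is that d = 0.40 is well chosen. The two trials are described as very similar Dutch self-help interventions, and the section on therapeutic approaches cites d = 0.40 for motivational interviewing on drinking (interval 0.17 to 0.70). This stands as a defence of the value as reasonable. It does not make it conservative.

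A third reply is that sizes may be adjusted if necessary, which could also mean an increase, and that the example speaks of not fully compensating, so 68% and 66% are the extreme. Both statements are right. Still, the only example given is a reduction, and it is not tied to a drop-out rate actually observed.

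A reader might go further and infer that the planned effects lie far above the evidence cited. The documents do not support that:
- **Smoking:** the relative risk of 2.1 lies within the printed 2.05 to 2.20 (2.00 to 2.30 if recomputed from the printed quit rates 30%/15% and 23%/10%). The 10% control rate is the lower of the two in the trials from which the section derives its rates, and this raises the sample size.
- **Web versus print:** the cancer-survivor result in the Background ("web-based: 16.5%, print-based: 15.5"%) compares two versions of an active programme at 15 months in young adult and childhood cancer survivors. It says nothing about an interactive programme against a static information page at 6 months.
- **Alcohol:** the gap cannot be measured, because small has no figure.

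**Conclusion.** The point holds as a correction of a stated property. The design is not conservative at its planned effects: power is 80% for alcohol and about 78% for smoking at the printed rates (80% if the rate is read as 21.3%). The alcohol effect is a favourable but defensible choice from the cited evidence. Giving up the drop-out allowance could cost up to 12 percentage points in each trial (80% to 68%; 78% to 66%) if the planned 25% is lost.

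These figures rest on two-sided 5% tests of the two arms at 6 months, complete cases, and no gain from covariates, repeated measures or imputation. The results at smaller effects rest on assumed values. It does not follow that a null result is likely, or that the smoking effect was inflated.

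**What to change.** In the Sample size section:

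1. Delete the sentence calling the power analyses conservative.
2. State instead that the trials have about 80% (alcohol) and 78% (smoking) power at d = 0.40 and at 21% versus 10% respectively, and less at smaller effects. Alternatively, correct the smoking rate to 21.3%, which makes 157 per arm and 80% power agree.
3. Remove the example of not compensating drop-out, or make it conditional: the allowance may be reduced only if drop-out observed in the trial is shown to be below 25%, with the total recalculated as net size / (1 − observed drop-out) so that 99 and 157 per arm are still analysed.
4. Optionally, add a short table of power at smaller effects, labelled as assumptions.

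The cost is a few sentences of protocol wording, a slightly less favourable stated figure for the smoking trial, and loss of the option to under-recruit. No extra participants are requested.

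### The optional half-way power check may change the sample size with no restriction to pooled data, so the 5% level and 80% power are not assured

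*Protocol article*

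**What the plan says.** All of this is in the protocol article.

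- **Sample size, error rates.** For both trials, "conventional power (1-beta = .80) and levels of statistical significance (alpha = .05) are chosen".
- **Sample size, AM.** A "d effect size of d = 0.40 is expected", giving a "minimum net sample size of 2 × 99 participants in case of 2-sided testing, or 2 X 78 participants in case of 1-sided testing". With 25% non-response the two-sided enrolment is 264. Neither an SD nor a raw difference in drinks is given.
- **Sample size, SC.** "This translates into a 21% quit rate in the experimental condition", "assuming a 10% quit rate in the control condition at 6 months post-randomisation". The net size is 157 per arm (two-sided), and enrolment is 419 at 25% non-response.
- **Sample size, closing paragraph.** "We may perform half-way post-hoc power analyses for both RCTs, based on those we will evaluate our assumptions underlying these power calculations"; the sizes may then be adjusted. The one example is "We might for example not fully compensate the expected 25% drop-out, as drop-out rates might be lower", with partial recovery of power by multiple imputation as a second reason.
- **Randomisation.** In this open-label design, "the participants nor the researchers are blinded regarding the allocated conditions".

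**The concern.** The assumptions open to re-checking are mostly treatment effects. In AM they are d and the non-response rate. As no SD or raw difference is stated, a pooled SD has nothing to be compared with, and d can be checked only by comparing arms. In SC they are two arm-specific quit rates. Post-hoc power ordinarily means power at the observed effect. The natural reading of the permission is therefore a comparison of arms half-way, by people who know the allocation, followed by a new sample size and an ordinary final test. A size that depends on the interim effect raises the type I error of an unadjusted test.

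The drop-out example raises a separate question of power. If the allowance is reduced and attrition turns out as planned, fewer outcomes are observed than the calculation requires. Imputation restores only as much as the available data predict about the missing 6-month outcome.

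At stake is whether the final test has its stated properties, and whether a reader can tell a planned size from a results-driven one.

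**Working it through.** **1. Reproducing the plan's sizes** (two-sided 0.05, power 0.80, from Sample size)

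- AM, two-sample t-test, d = 0.40: 99 per arm; 2 × 99 / 0.75 = 264. Reproduced.
- SC, arcsine effect size h = 2·asin√p₁ − 2·asin√p₂. Exactly 21% against 10% gives h = 0.309 and 165 per arm. The mean of the three relative risks quoted, (2.14 + 2.05 + 2.20)/3 = 2.13, gives 21.3%, h = 0.316 and 157 per arm; 2 × 157 / 0.75 = 419. The stated size thus reproduces with the unrounded rate. At exactly 21%, 157 per arm has 78% power.

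**2. Type I error if the size is reset from the observed effect** (AM)

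Setting: a look at half of 99 per arm; new size per arm n = 2·((1.96 + 0.84)/d_obs)², held within limits; then an unadjusted two-sided z-test on all data. The true effect is zero, with at least 1,000,000 simulated trials per rule. The article sets no limits on the size, so those below are assumptions.

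| Limits on n, relative to 99 | Type I error |
|---|---|
| 0.75 to 1 | 5.5% |
| 0.5 to 1 | 5.8% |
| 0.75 to 1.33 | 5.9% |
| 1 to 2 | 6.0% |
| 0.5 to 2 | 6.8% |
| 0.5 to 4 | 7.4% |

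With the size fixed at 99 the same simulation returns 5.0%.

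**3. Type I error if only blinded variance is used**

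Same look, n recalculated from the pooled SD with the target difference held fixed, limits 0.5 to 2: type I error about 5.1%, power about 80.5%. A change driven only by the pooled response rate does not use the treatment effect either.

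**4. Power if drop-out is under-compensated** (two-sided, observed cases only, SC at exactly 21% against 10%)

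Observed per arm = enrolled × (1 − loss)/2.

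- Allowance removed, 25% loss. AM: 198 × 0.75 / 2 = 74.25, power 68%. SC: 314 × 0.75 / 2 = 117.75, power 66%.
- Allowance halved, 25% loss. AM: 198 + 66/2 = 231, 231 × 0.75 / 2 = 86.6, power 74%. SC: 314 + 105/2 ≈ 366, 366 × 0.75 / 2 = 137.25, power 72%.
- Allowance removed, smaller loss. AM: 80% at no loss, 76% at 10%, 71% at 20%. SC: 78%, 74% and 69%.
- Allowance kept, no loss. AM 90%, SC 88%.

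**5. What imputation could return** (AM, allowance removed, 25% loss)

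Approximate effective size per arm = 74.25 + 24.75 × f × r², where f is the share of drop-outs with a usable predictor and r its correlation with the 6-month outcome (both assumed).

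- f = 0.5, r = 0.6: 74.25 + 4.5 = 78.7, power 70%.
- f = 1, r = 0.7: 74.25 + 12.1 = 86.4, power 74%.

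**The case against.** The step is optional twice over: the check may be done, and the size may be changed. No section says that outcomes will be compared by arm half-way. Researchers who know the allocation in an open-label trial can still review pooled data. The only trigger named is drop-out, and changing enrolment on that ground does not inflate type I error. The larger figures need effect-driven increases to two or four times plan, which the article nowhere mentions. The text speaks of not compensating in full, partly because drop-out may be lower, and claims only partial recovery from imputation. Baseline measures can inform the imputation too. A journal article may also leave the mechanics to a fuller document.

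Much of this stands. A reader might infer that neither the 5% level nor the 80% power holds, or that the attrition allowance will be dropped. The documents support neither: both outcomes depend on how an optional permission is used. Nor should the smaller one-sided sizes be used to enlarge the error figures. A one-sided test at 0.05 has 5% false claims of benefit by construction, and that is a question of sidedness. A ban on every reduction would also go too far, since lowering enrolment when pooled attrition proves low is legitimate.

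What does not fall away is the permission itself. It is more than omitted detail: the article states an open option to resize on re-checked assumptions, and those are mainly between-arm effects.

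**Conclusion.** The point holds in conditional form: the 5% level and 80% power are not assured under the text as written.

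- **Level.** It is inflated only if the size is changed on the observed between-arm effect and the final test is unadjusted. The size is then about 5.5–6.0% when one limit stays at plan or the range is narrow, and 6.8–7.4% with limits of half to two or four times plan. These rest on assumed limits, a look at half the AM net size and resetting to 80% power at the observed effect.
- **Power.** It falls short only if the allowance is cut by more than actual attrition permits. With the planned 25% loss, AM has about 74% with the allowance halved and 68% with it removed; SC has 72% and 66%. SC starts from 78% at 157 per arm for exactly 21% against 10%, so not all of its shortfall comes from the allowance. Imputation would recover part of the loss.

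The inflation is modest, but it affects the primary test of both trials and is avoidable by wording. The change should be made.

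**What to change.** Replace the half-way post-hoc power analyses with a blinded sample-size review.

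- Limit it to the pooled 6-month response rate, the pooled SD of drinks (AM) and the pooled quit rate (SC).
- State the raw difference in drinks that d = 0.40 represents; without it a pooled SD cannot be turned into a sample size.
- Compute no between-arm effect before the final analysis.
- Allow enrolment to be lowered only on the pooled response rate, and only if the expected observed numbers stay at or above the two-sided net targets (99 per arm in AM, 157 in SC).
- Remove expected gains from imputation as a reason for not compensating drop-out.

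The cost is wording, one added figure for AM, and the loss of the freedom to change the trial size on an interim effect. A legitimate saving when attrition is low remains available.
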